#### Statistical power and sample size considerations for primary objectives

Given our focus on participant engagement and the intricate nature of the study design, we opted for a simulation-based approach to ascertain the appropriate sample size and statistical power [75]. We generated data for a 16-cluster randomised experiment with eight unique experimental conditions, varying the number of participants within each cluster (mean of 40, standard deviation of 8). We built the analysis model outlined above for each of the primary outcomes (i.e., overall app launches, proportion of sessions completed, and proportion of home practice activities started), estimating engagement rates and model parameters based on existing digital parenting intervention research (e.g., [32]), digital mental health interventions implemented in real-world settings (e.g., [36]), the original PLH for Teens cluster RCT in South Africa [13], and plausible scenarios based on observations from the ParentApp feasibility pilot. For each outcome model, 10,000 datasets were generated.

We estimated the minimum effect sizes needed to achieve ≥ 80% power for each of the primary outcomes while taking into account clustering and assuming an alpha level of 0.05. Poisson and Binomial distribution models were fitted for count and factor outcomes, respectively. Effect sizes were calculated as incidence rate ratios (IRRs) for Poisson distribution models and odds ratios (ORs) for Binomial distributions, which were averaged across all 10,000 replications. For overall app launches, the mean IRRs were 1.14 for support (WhatsApp), 0.91 for app design (sequential workshops), and 1.21 for digital literacy (on). For the proportion of sessions completed, the mean ORs were 2.18 for support (WhatsApp), 0.48 for app design (sequential workshops), and 2.35 for digital literacy (on). For the proportion of home practice activities started, the mean ORs were 3.13 for support (WhatsApp), 0.67 for app design (sequential workshops), and 2.31 for digital literacy (on). Based on these results, we determined that a sample of 640 participants would be sufficient to detect a significant effect in each of the primary outcomes.

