During the Preparation Phase, we conducted surface adaptations from the in-person PLH for Teens programme implemented in Tanzania [53], including condensing content from 14 to 12 sessions and using culturally appropriate illustrations that were gender-neutral, amorphous cartoon figures. Subsequent stages included iterative user testing with caregivers and adolescents from nine LMICs [54]. Results from the user testing demonstrated high satisfaction and acceptability of content. However, participants’ views on the app’s animated cartoons varied, with some finding them too juvenile. Participants also highlighted the need for regular reminders to encourage engagement. Following feedback from the user testing, we conducted a pilot study of intervention feasibility when delivered as a self-guided programme in low-income communities in South Africa. Findings from the pilot with 107 caregivers and nine implementing staff support those from the user testing; that the content is acceptable, relevant, and useful, and that the app is easy to use. Nevertheless, participant engagement in the pilot was low, with as little as 25% of recruited participants still engaging after the first session. Technical challenges and internet access were cited as some of the main difficulties for participants. Other feedback included wanting flexible access to content, and an alternative interface with human images. Participant feedback also suggested the need for an element of regular human support. Several adaptations were made following these findings and are being piloted in Tanzania, including testing the feasibility of remote support via one-on-one phone consultations and moderated WhatsApp groups.

Findings from the Preparation Phase as well as the larger digital intervention literature guided the selection of intervention components to be tested in the multifactorial experiment (see conceptual model in Fig. 1). The following criteria were used for component selection: each component must address at least one theoretical mediator associated with engagement with digital parenting interventions; each component must be unique from other components in terms of delivery mode, approach, or content; each component must contain at least some initial evidence in the literature; and each component and component level must be relatively low-cost and feasible for implementation in low-resource settings.

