
##### Mitigating potential harm from intervention

We have also considered the potential risk of harm from participating in the intervention, and will be monitoring this throughout the project [79]. Participation in the parenting programme may potentially cause psychological harm for caregivers, particularly when they confront difficult experiences from their own childhood or deal with intimate partner violence at home. However, past research on parenting interventions, including numerous randomised trials conducted in LMICs [11], have consistently shown no evidence of harm and abundant evidence of benefits for both parents and children, as well as high levels of parent satisfaction. To ensure a comprehensive understanding of the potential outcomes of the parenting programme, this study will explicitly examine both the benefits and risks of the intervention. Our statistical analysis plan includes two-tailed tests to assess the differences between groups and examine potential positive and negative effects of the intervention. We will also use qualitative analysis to explore the experiences and perspectives of participants regarding the intervention and its effects.

We anticipate no direct harm as a result of withdrawing from the intervention, as participation in the programme is completely voluntary, with no direct penalties for non-participation. Furthermore, other studies, including evaluations in other low-resource settings [11], have shown no evidence of harm resulting from the termination of parenting interventions. In the unlikely event of significant harm being observed in any of the intervention conditions, we will suspend the implementation of the programme until the harm has been adequately addressed, and the programme has been modified accordingly.

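### The app-launch and home-practice effects cannot all be minimum effect sizes for 80% power, so as labelled they do not support the statement that 640 participants are enough

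*Protocol article*

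**What the plan says.** The section on statistical power and sample size describes a simulation of 16 clusters and eight conditions, with 10,000 datasets per outcome. It labels the result: "We estimated the minimum effect sizes needed to achieve ≥ 80% power for each of the primary outcomes". It then gives three values for each primary outcome, one per component. For launches: "For overall app launches, the mean IRRs were 1.14 for support (WhatsApp), 0.91 for app design (sequential workshops), and 1.21 for digital literacy (on"). For home practice: "the mean ORs were 3.13 for support (WhatsApp), 0.67 for app design (sequential workshops), and 2.31 for digital literacy (on"). For sessions completed the odds ratios are 2.18, 0.48 and 2.35. From these it concludes: "we determined that a sample of 640 participants would be sufficient to detect a significant effect in each of the primary outcomes".

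The overview of the study and Table 1 place two clusters in each of the eight conditions. They say that each component is assessed by setting all caregivers at one level against all at the other. The analysis section fits one mixed model per outcome with a random intercept for neighbourhood.

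**The concern.** A minimum detectable effect is fixed by the standard error, the significance level and the power. If three contrasts in one model have the same standard error, they have the same minimum on the log scale, apart from sign. Three clearly different values cannot all be minima.

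The selection strategy for the final package makes this matter. A component without a main effect falls back to the lower level or to the level expected to do worse. App design has the smallest listed effect on all three outcomes, so it is the component most exposed to a false negative that is carried into the next trial. A reader of the article cannot tell what power it has.

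**Working it through.** **Inputs from the protocol.** Significance level: "assuming an alpha level of 0.05". Two-sided testing, from the section on mitigating harm: "Our statistical analysis plan includes two-tailed tests to assess the differences between groups". Power 80%. Each component compares 8 clusters with 8, about 320 caregivers with 320; mean cluster size is 40. Base rates and between-neighbourhood variance are not stated in the article. The 640 and its 80% power can therefore be neither reproduced nor refuted.

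**Step 1: size of the listed effects on the log scale.**

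| Outcome | Support | App design | Digital literacy | Largest / smallest |
|---|---|---|---|---|
| App launches | 0.131 | 0.094 | 0.191 | 2.02 |
| Sessions completed | 0.779 | 0.734 | 0.854 | 1.16 |
| Home practice | 1.141 | 0.400 | 0.837 | 2.85 |

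**Step 2: standard error each value needs to be a minimum.** Minimum |log effect| = (1.960 + 0.842) × SE = 2.8016 × SE, so SE = |log effect| / 2.8016.
- Launches: 0.047, 0.034, 0.068.
- Sessions: 0.278, 0.262, 0.305.
- Home practice: 0.407, 0.143, 0.299.

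**Step 3: can the standard errors differ that much?** A linearised random-intercept model was run on the 16-cluster layout with cluster sizes of mean 40 and SD 8. The assumed ranges were baseline proportions 0.02 to 0.50 with cluster SD 0 to 0.8 (logit scale), and mean launches 5 to 40 with cluster SD 0 to 0.3 (log scale). Within an outcome, the components' standard errors differed by about 1.00-fold for launches. For home practice they differed by at most 1.12-fold, mostly 1.03 or less. The labels need 2.02 and 2.85.

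**Step 4: other explanations.**
- *Averaging ratios over replications.* With mean ratio = exp(b + SE²/2), the SEs needed become 0.046, 0.034, 0.067 (launches) and 0.381, 0.147, 0.284 (home practice). The spread remains.
- *Rounding.* The least spread that rounding allows is ln 1.205 / |ln 0.905| = 0.186 / 0.100 = 1.87 for launches, and ln 3.125 / |ln 0.665| = 1.139 / 0.408 = 2.79 for home practice.
- *Direction.* Effects in the same direction differ too: 1.14 against 1.21, and 3.13 against 2.31.

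**Step 5: what the list implies if the smallest effect per outcome has 80% power.** Power = Φ(|log effect| / SE − 1.96).

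| Outcome | SE | Common minimum | Power: support, app design, digital literacy |
|---|---|---|---|
| Launches | 0.034 | IRR 1.10 or 0.91 | 97%, 80%, >99.9% |
| Sessions | 0.262 | OR 2.08 or 0.48 | 84%, 80%, 90% |
| Home practice | 0.143 | OR 1.49 or 0.67 | >99.9%, 80%, >99.9% |

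**Step 6: variation this allows for launches.** With 8 against 8 clusters, SE² = SD² × (1/8 + 1/8), so SD = 2 × SE. For IRR 0.91, SD = 2 × 0.0337 = 0.067 (0.062 with a t-test on 12 df). This is the total SD of neighbourhood log-means, including sampling of persons. With no true neighbourhood variance and 40 persons per cluster, the person-level coefficient of variation could be at most 0.067 × √40 = 0.43 (0.39 with 12 df). If the total SD were 0.10, SE = 0.05 and power for 0.91 is 47% (41% with 12 df). For home practice, OR 0.67 allows a total SD of 2 × 0.143 = 0.29 on the logit scale (0.26 with 12 df).

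**Step 7: sensitivity for launches.** Assumptions: mean 20 launches, no neighbourhood variance, person-level coefficient of variation CV beyond Poisson noise, SE² = 2 × (1/20 + CV²) / 320, 12 df.

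| CV | SE | IRR 0.91 | IRR 1.14 | IRR 1.21 |
|---|---|---|---|---|
| 0.3 | 0.030 | 83% | 98% | >99% |
| 0.5 | 0.043 | 52% | 79% | 98% |
| 1.0 | 0.081 | 19% | 32% | 58% |

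**The case against.** The strongest reply is that the text promises at least 80% power, not exactly 80%. If the smallest effect for each outcome reaches 80%, the others exceed it, and 640 is adequate for all nine listed effects (step 5). That stands. It saves the sample size as a possibility but not the label: on this reading 1.14, 1.21, 3.13 and 2.31 lie well above the minimum.

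A reader might infer that 640 is too few. One route is to place the largest effect at 80%, which leaves 28% power for IRR 0.91 and 16% for OR 0.67. That reading puts listed effects below the stated 80%, so the text contradicts it. Another route is the pilot, where "as little as 25% of recruited participants still engaging after the first session". This points to uneven use, but the pilot was a self-guided one in South Africa, adaptations followed, and the article gives no launch counts, means or variances from it. The rows of step 7 rest on assumed inputs and lead either way.

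It is also fair that the sessions odds ratios are nearly consistent, that the Poisson and Binomial distributions are named only as examples, and that a condensed article may leave base rates and cluster variance to a fuller document. Their absence is not the point here. The article itself states the nine values, labels them and draws its sample-size conclusion from them.

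**Conclusion.** The label is wrong for two of the three primary outcomes. The launch values spread 2.02-fold and the home-practice values 2.85-fold on the log scale, while the components' standard errors are nearly equal. This follows from the balanced layout; the only assumptions are the wide ranges in step 3. The sessions values, at 1.16-fold, are close to a common minimum. That the listed values are assumed scenario effects is the likeliest explanation, since the section says that parameters came from earlier research and plausible pilot scenarios, but the text does not say so.

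The sufficiency of 640 is therefore not supported by the figures as labelled. It is unverifiable, and the documents do not show it to be false. The limit of about 0.067 on the SD of neighbourhood log-means is a demanding condition given uneven engagement in the pilot. It is a sensitivity point and not proof of low power.

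**What to change.** 1. Relabel the launch and home-practice values as assumed effects.
2. From the existing simulation, report the achieved power for each component and outcome.
3. Give one minimum detectable effect per outcome that applies to all three components, stated in both directions.
4. Add a sensitivity run with person-level overdispersion and a range of between-neighbourhood variance, most of all for launches.
5. Restate the sentence on 640 participants so that it matches these results.

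The cost is a small rerun of existing code and some restated figures, which may be less favourable. No participants or clusters are added, and the planned analysis of the trial does not change.

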#### Exploratory analyses

##### Objective 3: To conduct exploratory analyses to examine whether there are any interaction effects between components on primary and secondary engagement outcomes

We anticipate that there will be some interactions (synergistic effects) between component levels. In exploratory analyses, we will examine a fully saturated generalised linear mixed effects model which includes all three main component effects, as well as two-way and three-way interactions. This model will be replicated for each of the primary and secondary outcomes. However, interaction effects will not be considered in the final component level selection process due to potential power constraints.

##### Objective 4: To conduct exploratory analyses of the potential impact of components and combination of component levels on caregiver behavioural outcomes (e.g., child maltreatment, positive parenting, parental communication about sexual abuse prevention)

Engagement is a precursor to behaviour change. We will therefore investigate whether experimental components designed to enhance engagement also impact caregiver behavioural outcomes at post-intervention. Using the same generalised linear mixed effects models outlined above, we will examine the main and interaction effects of intervention components on the core ParentApp targets: reducing child maltreatment, improving positive parenting and supervision, and increasing parental communication about sexual abuse prevention. Covariates will additionally include baseline assessments of each outcome. We may also conduct exploratory mediation analyses to generate learning around which engagement variables mediate programme impacts.

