### Digital interventions as a scalable alternative

With the rapid increase in technology and internet access in LMICs, adaptation of parenting programmes into digital formats has the potential to overcome some of the prominent limitations associated with in-person delivery. Digital parenting programmes, i.e., parenting interventions that use digital technologies to promote behaviour change [27], can be delivered remotely via various platforms including smartphone applications (apps), chatbots, social media, and websites, and range from guided delivery with human support to completely self-guided [28]. These delivery formats may allow for greater scalability, can be accessed irrespective of location and time, and may allow LMICs or underserviced areas to deliver programmes that would otherwise be too costly.

A small but growing number of digital parenting programmes have been tested in high- and middle-income countries to date, with meta-analytic and systematic reviews from high-income countries indicating that they may yield effects comparable to in-person parenting interventions (e.g., [28–33]). However, a major concern that prevents their successful implementation is low engagement by parents. For example, only 7.5% of parents who enrolled in a self-guided online parenting programme in Australia completed all core modules and post-intervention assessments [34]. Looking at the digital intervention literature more broadly, approximately 48% of participants drop out of smartphone mental health intervention trials before the end of data collection [35]. Retention rates are estimated to be even lower in real-world settings. For example, a systematic review investigating real-world uptake and engagement of digital self-help interventions found that while 21% to 88% of participants used the intervention at least once or completed one assessment or module; only 0.5% to 28.6% completed the intervention [36].

As a precursor to behaviour change, poor engagement in parenting programmes may compromise intervention effectiveness [37]. Consequently, low engagement has significant negative implications for population-level public health benefit. Therefore, optimising engagement strategies for digital parenting programmes is crucial to realise their full preventative potential and address the widespread issue of VAC in LMICs.

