#### Component B: app design (sequential/non-sequential)

In-person parenting programmes, including PLH for Teens, typically deliver sessions in a sequential, weekly basis. ParentApp was originally designed to mirror this structure, i.e., content is delivered in a sequential order, whereby a new workshop is made available once every programme week. However, qualitative findings from the pilot study in South Africa indicated that some participants wanted to access content more flexibly and at their own pace. In addition, findings from this pilot suggested that participants typically used the app in multiple, short sessions. This suggests that a short, task-based approach may be an acceptable mode of delivery. Previous studies of digital parenting programmes have used both sequential access (e.g., [58, 59]) and open access methods (e.g., [60]). However, none have investigated which approach is more effective at engaging and retaining participants.

To better understand the impact that sequential versus non-sequential access to content has on engagement, we will test two versions of the app: 1) a workshop-based design where participants access content in a sequential and timed-bound manner, and 2) a module-based design where content is broken down into smaller tasks and participants can access content in a non-sequential manner. Thus, participants will be randomised across two component levels: 1) sequential workshop-based design and 2) non-sequential modular design. Based on participant feedback in the Preparation Phase, these two designs also differ visually: the sequential design will retain the amorphous cartoon figures and the non-sequential design will incorporate human-like illustrations.

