**Fig. 2 Fig2:**
[figure not shown]
Study flow diagram

Potential caregivers will be invited to attend an in-person onboarding session where they will be screened for eligibility. Recruitment will continue until full study enrolment of an estimated 40 caregivers is achieved per cluster (October to December 2022). If necessary, recruitment will include peer-to-peer referrals in the community. At onboarding sessions, participants will provide informed consent and receive assistance to install and download the app on their smartphones from trained research assistants. Those who provide informed consent will be considered enrolled. They will then complete the self-administered embedded baseline assessment with support from the trained research assistants. At the end of the onboarding session, digital literacy training will be provided to participants in select clusters. Participants receiving moderated WhatsApp groups will be added to a group within the first week of enrolment. Post-assessments will be completed by participants on their smartphones approximately three months after baseline (January to March 2023) without the presence of a trained research assistant.

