### Data collection

Data collected will include digitally tracked engagement data, embedded questionnaire questions, and semi-structured qualitative interviews or FGDs. Questionnaire data includes sociodemographic and pre-post caregiver behavioural questions which are integrated into the first and the last ParentApp workshops/modules. Participants will complete the baseline assessment at the onboarding session, where they can seek support from research assistants. Research assistants have received extensive training from study investigators on interviewing techniques, ethics, and informed consent. All measures will be translated from English to Kiswahili and back translated. Cost data will be collected by research assistants, programme facilitators, coaches, and field coordinators throughout the study.

Interviews and FGDs will be conducted by local researchers with a subsample of participants following semi-structured interview guides. The interview guides are designed to facilitate discussion but remain flexible, allowing for the inclusion of emerging themes during data collection. Interviews and FGDs will be audio-recorded in addition to researchers taking backup notes. Before recording, permission will be sought from all participants, and in situations where the participants decline, notes will be taken. In cases where in-person interviews and FGDs are not possible, remote interviewing via telephone will take place.

Collecting digital engagement data in this trial requires participants to access the internet regularly so that their app activity data can sync with the online server. To improve the quality and accuracy of the data collected, we will provide participants with small monthly data bundles (approximately 1 GB). Additionally, to promote participant retention, participants who complete the questionnaire and semi-structured interview or FGDs will receive compensation for their time (approximately $2 per assessment).

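### The behavioural endline is built into the last workshop or module, so whether it is observed can depend on the randomised components, and Objective 4 may compare differently selected caregivers

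*Protocol article*

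**What the plan says.** Objective 4 sets the aim: "We will therefore investigate whether experimental components designed to enhance engagement also impact caregiver behavioural outcomes at post-intervention". It uses the same mixed models as the engagement analyses, adds the baseline value of each outcome as a covariate, and allows exploratory mediation through engagement variables.

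The Data collection section describes the instrument as "pre-post caregiver behavioural questions which are integrated into the first and the last ParentApp workshops/modules". The two ends are collected differently. For the first, "Participants will complete the baseline assessment at the onboarding session, where they can seek support from research assistants". For the second, the Participant timeline section says "Post-assessments will be completed by participants on their smartphones approximately three months after baseline", with no research assistant present.

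The two app versions release content differently (Component B). In the sequential version, "content is delivered in a sequential order, whereby a new workshop is made available once every programme week". The other is "a module-based design where content is broken down into smaller tasks and participants can access content in a non-sequential manner".

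The Hypotheses section expects each of the three components to change engagement. Other engagement measures treats engagement with the embedded endline as a study outcome in its own right. The Data analysis section plans intention to treat, inspection of missingness patterns, and multiple imputation by fully conditional specification where appropriate.

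**The concern.** Baseline is secured at onboarding. The endline sits in a unit that a disengaged caregiver may never open. If a component works as hypothesised, it brings more caregivers to that unit, and those it adds are likely to be less motivated than those who would have got there anyway. Randomisation balances motivation across all enrolled caregivers, but not across those with an endline. If motivation also predicts parenting behaviour beyond the baseline score, a component with no effect on behaviour can show one, and the direction is against the more engaging level. Mediation is exposed too, because the mediator helps decide who has an outcome.

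Timing is a second, smaller matter. The protocol gives one time for everyone but places the questions in a unit that the two app versions release differently. Most behavioural items ask about the past month. If a caregiver answered them soon after enrolment, they would partly describe the period before the intervention.

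**Working it through.** **1. Denominator.** 16 clusters × 40 = 8 conditions × 80 = 640 caregivers, or 320 per component level. This matches the protocol.

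**2. How many might reach the last unit.** The protocol gives no expected endline response. Its Background section cites other programmes: "only 7.5% of parents who enrolled in a self-guided online parenting programme in Australia completed all core modules and post-intervention assessments", and a real-world completion range of 0.5% to 28.6%. Applied to 640:
- 0.5%: 640 × 0.005 = 3.2
- 7.5%: 640 × 0.075 = 48
- 28.6%: 640 × 0.286 = 183

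These figures give context and are not forecasts. They come from different sources, none of them ParentApp, and in the non-sequential version reaching the last module need not mean completing the programme.

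**3. Differential endline observation.** The odds ratio of 2.18 (Support, proportion of sessions completed, from the sample size section) serves as a stand-in for a component's effect on having an endline. With high-level odds = 2.18 × low-level odds:

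| Low level | High level | Endlines of 320 v 320 |
|---|---|---|
| 7.5% | 15.0% | 24 v 48 |
| 15% (assumed) | 27.8% | 48 v 89 |
| 28.6% | 46.6% | 92 v 149 |
| 50% (assumed) | 68.6% | 160 v 219 |

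**4. Bias when the component has no effect on behaviour.** Assumptions not in the protocol:
- Latent motivation U is standard normal and raises the log-odds of having an endline by 1, 2 or 4 per SD.
- U correlates ρ with the part of the endline score that the baseline score does not explain.
- Baseline and endline scores correlate 0.5.
- There is no clustering.

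Then bias ≈ ρ × √(1 − 0.5²) × (difference in mean U between levels, among those with an endline). Across the settings in step 3, mean U is lower at the more engaging level by 0.10 to 0.31 SD.
- Smallest at ρ = 0.2: 0.2 × 0.866 × 0.103 = 0.018 SD
- Largest at ρ = 0.4: 0.4 × 0.866 × 0.313 = 0.108 SD

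Simulation (3,000 runs per setting, analysis of covariance on caregivers with an endline, two-sided 0.05) gave:

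| ρ | Bias against the more engaging level | Rejection rate |
|---|---|---|
| 0 | about 0 | 4.5% to 5.4% |
| 0.2 | 0.02 to 0.06 SD | 5% to 8% |
| 0.4 | 0.04 to 0.11 SD | 5% to 17% |

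At an assumed ρ of 0.6 the bias was 0.05 to 0.17 SD.

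**5. What imputation does.** In a 2,000,000-record check the endline was seen only above an engagement threshold (about 14% v 25% observed). The complete-case bias was 0.05 SD at ρ = 0.2 and 0.09 SD at ρ = 0.4. Imputing from component levels and baseline scores alone rests on the same regression among those observed, so it keeps that bias. Adding logged engagement cut it to 0.004 SD or less, also at ρ = 0.6. That result relies on a linear relation extrapolated to low engagers, none of whom has an observed endline. With every caregiver observed, the bias was 0.000 to −0.001 SD.

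**6. Timing.** Twelve workshops released weekly put the last one at about week 12, which agrees with about three months. For the non-sequential version "participants can access content in a non-sequential manner". There the last module is undefined, and no time gate on the endline is stated.

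**The case against.** **The plan is not a bare completer analysis.** This stands. Intention to treat, inspection of missingness and multiple imputation are planned, and endline engagement will be reported. The choice of imputation variables can reasonably sit in an analysis plan that is not shown. The placement of the endline is fixed here, however, and imputation from baseline variables alone would not repair what the placement causes.

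**A reader might infer that the three-month statement and the last-unit statement contradict each other outright.** The documents do not support that. One gives timing and the other gives location, and in the sequential version they agree. Early completion in the non-sequential version is an inference, because the article does not say whether the questionnaire is gated.

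**A reader might take 2.18 as the plan's expected effect on endline response.** It is not. It refers to the proportion of sessions completed, and the sample size section presents it as a minimum effect for at least 80% power.

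**The bias is modest against sampling error.** Also true. With 48 v 89 endlines the standard error is about 0.866 × √(1/48 + 1/89) = 0.155 SD before clustering, above the largest bias at ρ = 0.4. With 160 v 219 it is about 0.09 SD, and the bias approaches one standard error. The payment of about $2 per assessment may raise response, but it does not detach the endline from the last unit.

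**Conclusion.** The concern holds in a limited form. The protocol places the behavioural endline where engagement governs access to it, and it hypothesises that the components change engagement. Endline availability can therefore depend on randomised components, and Objective 4 and any mediation analysis may compare differently selected caregivers. The planned imputation does not remove this unless it uses post-baseline engagement, and then only by extrapolation.

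A spurious component effect is possible, not certain. It is zero if motivation has no link with the outcome beyond the baseline score, and about 0.02 to 0.11 SD for correlations of 0.2 to 0.4. Those correlations, the strength of selection and the use of 2.18 are assumptions. It would be tempting to conclude that a more engaging component will look harmful; the documents do not support that, because they say nothing about this correlation.

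The consequence is confined to exploratory findings. The primary engagement outcomes are logged by the app. The selection procedure for the final package rests on main effects on engagement, cost-effectiveness and qualitative findings.

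**What to change.** 1. Take the endline out of the last workshop or module. Prompt every enrolled caregiver, whatever their progress, with a stand-alone questionnaire that opens at the same fixed time in both app versions, about three months after enrolment as the Participant timeline section states. This also reconciles that section with Data collection.
2. Report endline response by component level.
3. Include logged engagement, component levels and baseline scores in the imputation or weighting model.
4. State with Objective 4 and any mediation result that endline availability may depend on engagement.

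The cost is one app-configuration change, one more prompt to caregivers and a paragraph of analysis text, with no extra participants. Caregivers who never reopen the app would still be missing, so selection is reduced, not eliminated. Post-assessments were scheduled for January to March 2023, before the article appeared in June 2023. If that schedule was kept, items 2 to 4 still apply to this trial, and item 1 applies to the subsequent randomised trial.
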